**2.3.2 Known Potential Benefits**

- Immediate potential benefits include the identification of humoral immunodeficiency
- Long-term potential benefits include:
  - Decreased risk of non-neutropenic infection
  - Improved quality of life

**2.3.3 Assessment of Potential Risks and Benefits**

Subcutaneous Ig replacement therapy with Hizentra is generally well tolerated by patients with primary immunodeficiency, and generally has a better safety profile as compared to IV Ig replacement therapy. In the opinion of the investigators, the nominal risks of a laboratory evaluation followed by therapy with Hizentra are outweighed by the benefits of identification of humoral immunodeficiency in patients who otherwise remain undiagnosed. Identification of these patents will lead to therapy with subcutaneous Ig replacement, which may decrease the risk of non-neutropenic infection and potentially improve quality of life.

**3. Objectives and Endpoints**

1. The objective of this study is to identify patients with CLL who have serum IgG ≥400 mg/dL yet still have demonstrable humoral immunodeficiency.

To assess this objective, patients will undergo the following immune evaluation:

- Check serum IgG, IgM, IgA, IgE
- Check lymphocyte subsets, including CD4, CD8, CD3, and CD19
- Evaluate pre and post vaccine IgG responses 4 weeks apart to the following antigens: streptococcus pneumoniae, diphtheria, tetanus

Normal response to vaccination defined as follows:

- Strep pneumoniae (based on response to PPV)
  - If < 1.3, need to increase 2 fold to above 1.3 OR increase 4 fold
  - If > 1.3, need to increase 2 fold
  - Responses need to be demonstrated by 70% of serotypes
- Diphtheria, normal response
  - 2 fold increase into protective range
- Tetanus, normal response
  - 2 fold increase into protective range

Impaired vaccine response defined at abnormal response to any of the above antigens

2. Additional objectives of the study include to show that subcutaneous Ig replacement therapy is efficacious in increasing Ig levels and protective antibody titers in patients with CLL.

To assess this objective, IgG, IgM, IgA, IgE and IgG titers for streptococcus pneumoniae, diphtheria, tetanus will be checked periodically on therapy with subcutaneous Ig.

3. Another secondary objective will be to measure patient quality of life while on subcutaneous Ig replacement therapy.

To assess this objective, patients will complete SF-36 forms, which are a validated measure of patient quality of life.

**4. Study Design**

**4.1 Overall Design**

Hypothesis: By providing a novel approach to identifying CLL patients with humoral immunodeficiency by checking both Ig levels and vaccines responses., we will identify patients with impaired humoral immunity despite serum IgG ≥400 mg/d. In these patients with impaired humoral immunity, we will use subcutaneous immunoglobulin replacement to show this intervention will be well tolerated and increase Ig levels and protective antibody titers.

Phase of the trial: Phase 2

Trial Design: Single center, case series.

Methods used to minimize bias: Most of the endpoint are based on laboratory evaluation. The quality of life evaluation is a validated measure.

Dosing: Subcutaneous Ig replacement with Hizentra will be administered at 100 mg/kg/week, which is a typical dose used for Ig replacement in patients with immunodeficiency. The specific dose of Hizentra may be adjusted due to significant changes in weight during the study time period.

Study groups/arms: Patients with CLL will undergo a laboratory evaluation for impaired humoral function. All patients with an abnormal evaluation will all be offered therapy with subcutaneous Ig replacement. We plan to enroll 10 patients into the therapy portion of the study.

Single or multi-site study: Single.

Name of intervention: Hizentra

Interim analysis: An interim analysis is not planned at this time.

Study stratifications: There are no planned stratifications.

**4.2 Scientific Rationale for the Study**

Patients with CLL are at increased risk of infections as compared to age matched controls, with infections being a major cause of morbidity and mortality. Previous studies have shown that patients with CLL have both hypogammaglobinemia and impaired humoral immunity as defined by vaccine responses to both polysaccharide and peptide antigens. Attempts at decreasing infections in CLL have included therapy with prophylactic antibiotics and intravenous immunoglobulin. In general clinical practice and in previous studies, patients have started IV immunoglobulin replacement therapy if they have a history of serious infection or hypogammaglobinemia (defined as IgG below 400 g/dL). This study will provide a novel approach to identifying CLL patients with humoral immunodeficiency by checking both Ig levels and vaccines responses. In patients with impaired humoral immunity, we will use subcutaneous immunoglobulin replacement to show this intervention will be well tolerated and increase Ig levels and protective antibody titers. We hope this case series will lead to future studies with control groups and larger sample sizes.

**4.3 Justification for Dose**

Patients who qualify for subcutaneous Ig replacement therapy with Hizentra will receive a dose of 100 mg/kg/week, which is a typical dose used for Ig replacement in patients with immunodeficiency. As compared to primary immunodeficiency, patients with secondary immunodeficiency typically require lower doses of Ig replacement. A dose of 100 mg/kg/week falls on the lower end of the typical range for replacement dosing for Ig therapy.

**4.4 End of Study Definition**

A subject is considered to have completed the study if:

- They have a normal immune evaluation
- They have an abnormal immune evaluation and complete 6 months of therapy with subcutaneous Ig followed by the laboratory evaluation following a 3 month wash out period.

**5. Study Population**

**5.1 Inclusion Criteria**

In order to participate in this study, a subject must meet all of the following criteria:

- Diagnosis of chronic lymphocytic leukemia
- Medically stable, with expected survival of > 1 year
- Able to understand and willingness to sign a written informed consent
- Able to comply with study procedures

**5.2 Exclusion Criteria**

Any subject who meets any of the following criteria will be excluded from the study:

- Previously diagnosed primary immunodeficiency
- Additional immunosuppressive states as assessed by the primary or co-investigators
- Ongoing therapy with Ig replacement
- Serum IgG < 400 mg/dL

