**Objectives:**

*Primary objective:*

To identify patients with CLL with humoral immunodeficiency despite serum IgG ≥ 400 mg/dL

*Secondary objectives:*

1. Efficacy of subcutaneous Ig replacement therapy in increasing Ig levels

2. Efficacy of subcutaneous Ig replacement therapy in increasing protective antibody titers for diphtheria, tetanus, streptococcus pneumoniae

3. Safety and tolerability of subcutaneous Ig replacement therapy

4. Quality of life (SF 36) on subcutaneous Ig replacement therapy

5. Track the number of infections requiring antibiotics, further characterized per severity as defined in previous studies.

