**Participant Duration:**

The entirety of the study will entail 10 months (40 weeks) for each subject:

4 weeks of laboratory evaluation

24 weeks of subcutaneous Ig replacement

12 weeks of wash out period

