**1.3 Schedule of Activities**

Please see below.

|  | Screening | | Therapy with Ig Replacement | | | | | | | | | Wash Out Period | | | |
| --- | --- | --- | --- | --- | --- | --- | --- | --- | --- | --- | --- | --- | --- | --- | --- |
| Study visit | V1 |  | V2 | V3 | V4 | V5 | V6 | V7 | V8 | V9 | V10 | V11 | V12 | V13 | V14 |
| Week of study |  |  | 1 | 2 | 3 | 4 | 8 | 12 | 16 | 20 | 24 | 28 | 32 | 36 | 40 |
| Consent | X |  |  |  |  |  |  |  |  |  |  |  |  |  |  |
| Urine pregnancy test* | X |  |  |  |  |  |  |  |  |  |  |  |  |  |  |
| Medical history |  |  | X | X | X | X | X | X | X | X | X | X | X | X | X |
| Vitals |  |  | X | X | X | X | X | X | X | X | X | X | X | X | X |
| Physical exam |  |  | X | X | X | X | X | X | X | X | X | X | X | X | X |
| QoL (SF 36 form) |  |  | X | X | X | X | X | X | X | X | X | X | X | X | X |
| Pt teaching for Ig |  |  | X | X | X |  |  |  |  |  |  |  |  |  |  |
| Dispense study Ig |  |  |  |  |  | X | X | X | X | X | X |  |  |  |  |
| Pneumovax (PPV23) | X |  |  |  |  |  |  |  |  |  |  |  |  | X |  |
| Tetanus/diphtheria | X |  |  |  |  |  |  |  |  |  |  |  |  | X |  |
| IgG | X | X |  |  |  | X |  | X |  |  | X |  |  | X | X |
| IgM | X | X |  |  |  | X |  | X |  |  | X |  |  | X | X |
| IgA | X | X |  |  |  | X |  | X |  |  | X |  |  | X | X |
| IgE | X | X |  |  |  | X |  | X |  |  | X |  |  | X | X |
| IgG for 23 serotypes of strep pneumo | X | X |  |  |  | X |  | X |  |  | X |  |  | X | X |
| IgG for diphtheria | X | X |  |  |  | X |  | X |  |  | X |  |  | X | X |
| IgG for tetanus | X | X |  |  |  | X |  | X |  |  | X |  |  | X | X |
| T and B cell panel | X |  |  |  |  |  |  |  |  |  |  |  |  | X |  |

* Will be completed in women of child bearing age

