**2.2 Background**

Lymphoproliferative disorders (LPD) are one of the most common hematologic malignancies. Each year in the U.S., approximately 15,000 patients are diagnosed with chronic lymphocytic leukemia (CLL). [1] Patients with CLL are at increased risk of infections as compared to age matched controls. [2] Furthermore, infections remain a major cause of morbidity and mortality, with up to 17% to 50% of infections being fatal. [2-4] Infection type and occurrence in CLL are related to disease stage and treatment history. CLL carries a known increased risk of bacterial infections, but certain anti-neoplastic agents increase the risk of viral infections, while the Bruton kinase inhibitor ibrutinib may decrease rates of infection. [5] Attempts at decreasing infections in CLL have included therapy with prophylactic antibiotics and intravenous immunoglobulin. In general clinical practice and in previous studies, patients have started immunoglobulin replacement therapy if they have a history of serious infection or hypogammaglobinemia (defined as IgG below 400 g/dL). [4-8] Immunoglobulin replacement therapy has been shown to decrease rates of bacterial infection in some studies, but the utility of the universal application of the practice remains unclear. A Cochrane meta-analysis concluded that the use of IVIG may be considered in patients with LPD with hypogammaglobinemia and recurrent infection, but acknowledged that the studies are heterogeneous. [9]

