**7. Study intervention discontinuation and participant discontinuation/withdrawal**

**7.1 Discontinuation of Study Intervention**

Study intervention will also halt if patients experience a hypersensitivity reaction to the study drug. The study intervention will also be halted if there is any serious adverse event deemed related to the study drug by the study investigators. If the study intervention is halted, then pre and post vaccination titers will be obtained after subcutaneous immunoglobulin has been discontinued for 3 months. Infections will continue to be tracked through patient contact, the electronic medical record, and pharmacy data. Quality of life data will still be tracked through patient contact.

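### Section 5.2 excludes only ongoing Ig replacement and sets no interval since the last dose, so residual donor antibody could misclassify a recently treated patient at V1

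*Protocol*

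**What the plan says.** The primary objective in the synopsis is "To identify patients with CLL with humoral immunodeficiency despite serum IgG ≥ 400 mg/dL". Two of the exclusion criteria in Section 5.2 bear on it: "Serum IgG < 400 mg/dL" and "Ongoing therapy with Ig replacement". The second names no time since the last dose, and the inclusion criteria in Section 5.1 do not mention earlier Ig.

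Under Section 3, humoral immunodeficiency is judged from titers before and 4 weeks after vaccination. A normal result needs at least a 2-fold rise, with added conditions on the level reached (1.3 for pneumococcus, the protective range for diphtheria and tetanus). Failure on any one antigen counts as impaired.

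The second challenge is handled differently. If treatment is halted early, Section 7.1 says that "pre and post vaccination titers will be obtained after subcutaneous immunoglobulin has been discontinued for 3 months". For completers, Section 4.4 describes six months of therapy "followed by the laboratory evaluation following a 3 month wash out period", and the synopsis lists "12 weeks of wash out period". In the Section 1.3 schedule, therapy runs to week 24 and the vaccines are repeated at week 36.

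On usual care, Section 2.2 says that "patients have started immunoglobulin replacement therapy if they have a history of serious infection or hypogammaglobinemia".

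**The concern.** The same vaccines and assays are used twice. The second time, the patient has been off Ig for 3 months. The first time, which supplies the primary endpoint, the patient need only not be on Ig at that moment. Someone who stopped a few weeks earlier meets Section 5.2.

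That patient's V1 blood contains donor IgG, with two possible effects. Total IgG may read at or above 400 mg/dL when the patient's own level is below it. The pre-vaccine titer is also raised by antibody that decays before the 4-week draw, so the ratio understates the patient's own response. IgG of at least 400 together with an impaired response is exactly the primary endpoint event. Under Sections 4.1 and 5.4 it also leads to an offer of 24 weeks of study Ig, so both the reported frequency and an individual patient's allocation are at stake.

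**Working it through.** **The protocol's own interval.** Vaccination at week 36 minus end of therapy at week 24 = 12 weeks. This agrees with the 3 months in Sections 4.4 and 7.1. No corresponding interval exists before V1.

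**Assumptions, none of them from the documents.** Infused IgG decays exponentially with a half-life h of 21 to 30 days. The increments and titer shares below are chosen for illustration. The fraction remaining after d days is r = 2^(-d/h).

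| Time | h = 21 days | h = 30 days |
| --- | --- | --- |
| 4 weeks (d = 28) | 2^(-28/21) = 0.397 | 2^(-28/30) = 0.524 |
| 12 weeks (d = 84) | 2^(-84/21) = 0.063 | 2^(-84/30) = 0.144 |

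**IgG gate.** Measured IgG = own IgG + increment × r, where d runs from the last dose to V1.
- Own 350, increment 200, 4 weeks: 350 + 200 × 0.397 = 429 to 350 + 200 × 0.524 = 455. The patient passes a gate that should exclude.
- The same patient at 12 weeks: 350 + 200 × 0.063 = 363 to 350 + 200 × 0.144 = 379. Correctly excluded.
- Own 300, increment 200, 4 weeks: 379 to 405. The result depends on the half-life.
- Outside that half-life range: own 350, increment 300, h = 35 days, 12 weeks gives r = 2^(-84/35) = 0.189 and 350 + 300 × 0.189 = 407. The patient still passes.

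**Fold-rise.** Scale the V1 titer to 1, with half own and half infused. If the true own response is k-fold, the measured fold is 0.5k + 0.5r, where r is now the decay over the 28 days between draws.
- k = 2: 1.0 + 0.5 × 0.397 = 1.20 to 1.0 + 0.5 × 0.524 = 1.26. This fails the 2-fold rule.
- k = 4: 2.0 + 0.5 × 0.397 = 2.20 to 2.0 + 0.5 × 0.524 = 2.26. This still meets it.
- Break-even: 0.5k + 0.5r = 2 gives k = 4 − r, which is 3.48 to 3.60. With this infused share, true responses between 2-fold and about 3.5-fold read as less than 2-fold, and stronger ones do not.

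Because r < 1, the measured fold is always below the true fold for a patient who responds. The level part of the rule can work the other way: donor antibody can help a post-vaccine titer clear 1.3 or the protective cut-off. In a narrow band of moderate responders ending just under the cut-off, the error would be a false normal. The main direction is toward false impairment.

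**Effect of one false case.** The synopsis expects 10 treated of 20 to 30 evaluated, which is 50% or 33%. If one of the 10 should have been excluded at the gate, the rate becomes 9/19 = 47% or 9/29 = 31%. If that patient belonged in the study but was a true normal responder, it becomes 9/20 = 45% or 9/30 = 30%.

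**The case against.** The strongest defense is that nothing shows the group at risk is more than a handful. Section 2.2 says when Ig is started, not how often it is stopped. A patient who started and continues is already excluded. To cause trouble, a patient must have stopped within roughly the last 3 months, read at least 400 mg/dL, and enroll. The study is a descriptive proof-of-concept series without a hypothesis test (Sections 9.2 and 9.4), and one false case moves the rate by only 2 to 5 percentage points. This stands. It limits the size of the point but does not supply the missing interval.

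A second defense is Section 6.5, which rules out Ig from outside the study throughout. That sentence sits under concomitant therapy and refers back to the exclusion criteria, so it governs use during the study and sets no look-back. Investigator discretion over other immunosuppressive states does not cover recent Ig replacement either.

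Four stronger readings are tempting, and the documents do not support them.
- A reader might infer that the protocol requires 3 months off Ig before any vaccine titer and then breaks its own rule. The interval is stated for study SCIG before the end-of-study challenge. The same titers are deliberately drawn on therapy at weeks 4, 12 and 24 for another objective.
- A reader might infer that recently treated patients are to be expected in the source registry. No frequency is given.
- A reader might take the 2-fold example to mean that false impairment is general. That example sits exactly on the cut-off, and the 4-fold responder shows that the effect depends on response size and infused share.
- A reader might object that the entry and post-washout challenges cannot be compared. No listed objective, endpoint or hypothesis makes that comparison.

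**Conclusion.** The point holds as a gap in the eligibility wording. As written, Section 5.2 admits a patient with recent Ig exposure, and the V1 evaluation of that patient could produce a false primary endpoint event through the gate, the fold-rise, or both. What is established is the gap, the mechanism and its main direction. How often it would occur, and hence the size of the bias, is unknown. The figures of 40-52% remaining at 4 weeks, 429-455 mg/dL at the gate and 1.2-1.3-fold for a true 2-fold responder illustrate assumed half-lives, increments and shares. They are not estimates for this trial. The documents support saying that individual patients could be misclassified. They do not support saying that the primary endpoint as a whole is invalid.

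**What to change.** Reword the exclusion in Section 5.2 to: ongoing Ig replacement, or any Ig replacement within the 3 months before V1. This is the interval the protocol already uses before its end-of-study challenge. Because Section 6.5 refers back to Section 5.2, check that the two still read consistently. Record the date of the last dose of any earlier Ig, so that patients with past exposure can be identified in the individual data.

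The change reduces carry-over without removing it: under the assumed half-lives, 6-14% of infused IgG is still present at 12 weeks, and the 407 mg/dL case shows that a gate error remains possible under less favorable assumptions. It is an entry and measurement rule only and says nothing about whether any patient should receive or stop Ig.

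The cost is one line in Section 5.2 and one data field. A few candidates would be deferred or ineligible. Their number is unknown, but they are the same patients whose V1 results would otherwise be in doubt.

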**5.3 Lifestyle considerations**

There are no restrictions pertaining to lifestyle or diet due to this study.

**5.4 Screen Failures**

Due to the nature of this study, there will be no screen failures. All patients will CLL will be evaluated, with patients with an abnormal immune evaluation going on to the therapy phase of the study with subcutaneous Ig replacement. Patients will a normal immune evaluation will not be offered therapy with subcutaneous Ig replacement, but will be included in the study as well.

**5.5 Strategies for Recruitment and Retention**

The study will largely recruit from the hematology/oncology division at Rochester Regional Health. The majority of active CLL patients are enrolled in a registry, which will aid in identifying potential subjects. The registry has roughly 300-350 patients with CLL. Additionally, through professional networks and relationships, the study will also be advertised to other local hematology/oncology practices, each of whom have contributed patients in the past to previous research studies. In total, we expect to evaluate 20-30 patients to have 10 qualify for the therapy portion of the study with subcutaneous Ig replacement.

Once enrolled, subjects will be in close contact with the investigators and the clinical research support staff regarding the results of their laboratory evaluation, and if applicable, the administration of subcutaneous Ig replacement. For subjects being treated with subcutaneous Ig replacement, the first 2-3 visits will be done on site with the clinical research coordinator. If and when subjects are comfortable self-administering subcutaneous Ig therapy at home, the clinical research coordinator will be in phone contact at fixed intervals regarding tolerability of therapy. Subjects will also be asked to pick up supplies for Ig replacement on a monthly basis from the clinical research coordinator.

**6. Study Intervention**

**6.1 Study Intervention Administration**

**6.1.1 Study Intervention Description**

Hizentra 100 mg/kg/week x 24 weeks

**6.1.2 Dosing and Administration**

Each subject will be treated with a fixed dose of subcutaneous Hizentra 100 mg/kg/week for 24 weeks. Hizentra will be administered at the study site until patients are comfortable with self-administration at home. Typically, this will take 2-3 sessions on site with the assistance of the clinical research coordinator. Once patients are self-administering at home, they can administer at any time of day. There will be no defined relationship to administration of Hizentra in regards to meals. All subjects will discontinue Hizentra after 24 weeks of therapy, and will subsequently monitored for a 3 month wash out period. The specific dose of Hizentra may be adjusted due to significant changes in weight during the study time period.

Subjects will be advised regarding the following points regarding administration:

- Prior to administration, visually inspect each vial of Hizentra for particulate matter or discoloration, whenever the solution and container permit.
- Do not freeze. Do not use any solution that has been frozen.
- Check the product expiration date on the vial label. Do not use beyond the expiration date.
- Do not mix Hizentra with other products.
- Do not shake the vial.
- Use aseptic technique when preparing and administering this product.
- The Hizentra vial is for single-use only. Discard all used administration supplies and any unused product immediately after each infusion in accordance with local requirements.

Subjects will be advised regarding the following points regarding dosing:

- Hizentra is intended for subcutaneous administration using an infusion pump.
- Infuse Hizentra in the abdomen, thigh, upper arm, and/or lateral hip.
- Infusion sites – A Hizentra dose may be infused into multiple infusion sites. Use up to 8 infusion sites in parallel. More than one infusion device can be used simultaneously. Infusion sites should be at least 2 inches apart. Change the actual site of infusion with each administration.
- Volume (as tolerated) *–* For the first infusion of Hizentra, do not exceed a volume of 15 mL per infusion site. For subsequent infusions, the volume may be increased to 25 mL per infusion site.
- Rate (as tolerated) *–* For the first infusion of Hizentra, the recommended flow rate is up to 15 mL per hour per infusion site. For subsequent infusions, the flow rate may be increased to 25 mL per hour.

